### Perinatal data collection

An extensive record of the pregnancy, birth history, and neonatal course will be collected from the medical discharge summary. This will allow detailed description of the characteristics of the sample, allow comparison to outcomes establishing predictor variables, and to adjust for confounders.

A number of prenatal variables have been shown to impact short and long-term outcomes. Prolonged rupture of membranes, defined as spontaneous rupture of membranes ≥24 h before delivery is the most significant risk factor of a poor outcome among pregnancy history [94, 95]. Maternal antenatal corticosteroid administration reduces the risk of neonatal death and respiratory distress (complete course defined as more than 1 dose of steroids given, and 1st dose at more than 24 h and less than 8 days before birth) [94–96]. Evidence also exists for antenatal steroids protecting against cerebral haemorrhage [97]. The neuroprotective effect of magnesium sulphate administration reduces the risk of an outcome of CP (relative risk 0.68, 95 % confidence interval 0.54 to 0.87) [98]. Assisted conception is associated with adverse neurodevelopmental outcomes independent of prematurity, multiple pregnancy and gender for infants born between 22–26 weeks gestation [99]. Multiple birth status will be examined as the widely held view that singletons experience better outcomes than multiples has recently been challenged. In a population based study of *n* = 1473 born <29 weeks gestation, infants from multiple gestation pregnancies demonstrated comparable neurodevelopmental outcomes to singletons [100].

Birth history variables collected will include GA at birth, gender and birthweight. The risk of CP and adverse neurodevelopmental outcomes increases with decreasing GA at birth [101] and multiple studies report poorer outcomes for male infants [94, 102–104]. Intra uterine growth retardation (IUGR) can result in decreased cortical volume, poorer outcomes and increased risk of neonatal complications [105, 106] and babies that are small for gestational age (SGA) are at a higher risk of death, adverse neonatal outcomes and neurodevelopmental impairment [107]. Growth restriction in this study will be defined as a birth weight <10th percentile based on the Olsen growth curves.

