Information will be gathered over each infant’s neonatal course from birth until discharge from hospital. Cranial ultrasound findings, specifically findings of PVL and IVH graded according to the criteria of Papile et al., 1978 will be documented, with higher grades predictive of adverse outcomes and CP [108]. Necrotising enterocolitis (NEC) is associated with poorer growth, cognitive and motor outcomes and is considered proven if the infant warranted treatment which included nil by mouth and antibiotics [95, 109]. Late onset sepsis is a significant risk factor, diagnosed by isolation of an organism from at least one blood culture and a decision to give antibiotics with therapeutic intent, from 48 hrs after birth [94, 95]. Culture proven sepsis is independently associated with an outcome of CP [110]. Postnatal corticosteroid use demonstrates an independent effect on poor outcome, in particular with behavioural outcomes and CP [94, 111, 112]. Bronchopulmonary dysplasia or chronic neonatal lung disease are independent risk factors for adverse neurodevelopmental outcomes due to recurrent episodes of hypoxia [111, 113–117]. Chronic neonatal lung disease is defined as babies born <32 weeks GA requiring any respiratory support or supplemental oxygen for a chronic pulmonary disorder at 36 weeks PMA [95]. Postmenstrual age at NICU discharge will be documented, as poorer behavioural outcomes are associated with longer length of hospital stay [118].

For each infant from birth until 34 weeks PMA, the daily intake of all nutrient-containing solutions will be recorded. Intake of protein, lipid, carbohydrate and energy for each day will be calculated by multiplying intake volumes for each solution administered by the nutrient concentration obtained from manufacturers specifications or, for breast milk, published data [119].

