### Data analysis and statistical considerations

When models involve brain structure and function data from one time point (either 30–32 or 40–42 weeks), standard regression models will be constructed; when models use data from both 30–32 and 40–42 weeks, mixed-effects models that take into account within-infant correlation will be used. Models will be constructed using standard principles; first univariable analyses will be used to identify variables significant at the *p* < 0.15 level and these variables then entered into multivariable models one-by-one, in decreasing order of significance. At each step the current model will be compared to previous models using the likelihood ratio test. Linear regression will be used for continuous outcomes (e.g. diffusion MRI measures of FA and MD); logistic regression for binary outcomes (e.g. disability/no disability); and multinomial logistic regression for categorical outcomes with > 2 categories (e.g. NSMDA categories of normal/suspect/abnormal). Results will be presented as effect estimates and 95 % confidence intervals. The sensitivity and specificity of the predictive assessment model will be determined based on diagnosis of disability using standard definitions. Perinatal, clinical, demographic and social characteristics will be included as covariables when appropriate. Analyses will be supervised by [name], a senior biostatistician at The University of Queensland.

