## Discussion

To our knowledge, this protocol describes the first study examining the clinical correlates of early advanced brain imaging and clinical measures at 30 weeks PMA to predict motor and neurodevelopmental outcomes at 3 and 12 months CA.

The results of this study will i) establish the relationships between early clinical measures, EEG, perinatal variables and nutrition and early advanced neuroimaging at 30 weeks PMA, ii) establish which components of brain structure and function most accurately predict neurodevelopmental, motor outcomes and CP at 3 and 12 months CA, iii) accurately identify infants at risk of adverse outcomes at an earlier stage, introducing an additional window of opportunity for intervention, iv) contribute to understanding brain development between 30 and 40 weeks PMA, v) and develop robust quantitative biomarkers of brain maturation, which can then be used in the research of interventions in this population.

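### Accuracy is reported only for one selected model, so what 30-week MRI or examination adds to gestation, sex and cranial ultrasound is not secured

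*Protocol article*

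**What the plan says.** All references are to the protocol article.

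- **Data analysis and statistical considerations.** Candidates are screened univariably at p < 0.15, with "these variables then entered into multivariable models one-by-one, in decreasing order of significance". Then: "At each step the current model will be compared to previous models using the likelihood ratio test". No significance level for keeping a variable is given. On routine data: "Perinatal, clinical, demographic and social characteristics will be included as covariables when appropriate". These are neither named nor forced in. Accuracy is attached to one object: "The sensitivity and specificity of the predictive assessment model will be determined based on diagnosis of disability using standard definitions".
- **Perinatal data collection.** "Birth history variables collected will include GA at birth, gender and birthweight". Also recorded are "Cranial ultrasound findings, specifically findings of PVL and IVH graded according to the criteria of" a named scale, "with higher grades predictive of adverse outcomes and CP". The same section says that CP risk rises as gestation falls and that boys do worse.
- **Primary aims.** The third aim is prediction from MRI and functional measures. The fourth is prediction from perinatal variables and social risk. Neither is set against the other. The only stated comparison with other risk factors is the secondary aim on nutrition.
- **Discussion.** The study is expected to "accurately identify infants at risk of adverse outcomes at an earlier stage, introducing an additional window of opportunity for intervention", and to show which components of structure and function predict best.

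**The concern.** When the early scan is read, the unit already holds gestation, sex and the ultrasound findings to date, and the protocol itself treats these as predictors. The case for scanning and examining very preterm infants weeks before term depends on what the new measures add to that information.

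One sensitivity and one specificity for a model selected from a mixed pool cannot show this. If routine variables carry the model, their accuracy is published under the name of the predictive assessment model. If MRI happens to rank first, routine data are tested on top of MRI, and the question of interest, MRI on top of routine data, is tested only if both terms stay in. A single whole-model figure also cannot deliver the component ranking that the Discussion promises.

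**Working it through.** **1. What an added-value statement needs, against what is planned**

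| Needed | Planned |
|---|---|
| A fixed base of data known at the early scan | Perinatal and clinical covariables where appropriate, not named |
| Base entered first | Order set by univariable p-value |
| Test of early measures on top of the base | Likelihood ratio test against whatever model came before |
| Accuracy of base, of base plus early measures, and the difference | Sensitivity and specificity of one selected model |

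**2. The plan's own figure**

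Sample size section: 8 v 61 infants, CP 50 % v 5 %, alpha 0.05 (taken as two-sided), power 90 %.

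- Pooled proportion = (8×0.5 + 61×0.05)/69 = 7.05/69 = 0.102
- SE under the null = √[0.102×0.898×(1/8 + 1/61)] = 0.114
- SE under the alternative = √[0.25/8 + 0.0475/61] = 0.179
- z = (0.45 − 1.96×0.1139)/0.1790 = 1.267, so power = 89.7 %

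The stated 90 % reproduces. Expected CP cases are about 7 in 69, and 80×0.102 ≈ 8 in 80.

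**3. That contrast can arise with no added value**

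The documents give no ultrasound prevalence, overlap with MRI or ultrasound-specific CP risk, so these are assumptions. Let CP depend on ultrasound only, let ultrasound be abnormal as often as MRI (10/86), and let a share *o* of MRI-abnormal infants be abnormal on ultrasound. Then P(ultrasound abnormal | MRI normal) = 10(1−o)/76. Let *a* and *b* be the CP risks with abnormal and normal ultrasound. Solve o·a + (1−o)·b = 0.50 together with the matching equation for MRI-normal infants set to 0.05. For o = 0.8:

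- a − b = 0.45/(0.8 − 0.0263) = 0.582
- b = 0.5 − 0.8×0.5816 = 0.035
- a = 0.616

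| Overlap | CP risk, ultrasound abnormal / normal | MRI significant (unadjusted chi-square), n = 69, 6,000 runs |
|---|---|---|
| 70 % | 70.4 % / 2.3 % | 90.3 % |
| 80 % | 61.6 % / 3.5 % | 91.1 % |
| 90 % | 55.1 % / 4.3 % | 90.8 % |

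The last column is flat by construction, because MRI shows 50 % v 5 % at every overlap. Per 86 infants there are 10×0.5 + 76×0.05 = 8.8 CP cases. This MRI, with no information of its own, has sensitivity 5/8.8 = 57 % and specificity 72.2/77.2 = 94 %.

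**4. The stated stepwise procedure**

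Step 3 is not that procedure, so the procedure was simulated separately: screen at 0.15, enter by significance, keep on the likelihood ratio test at 0.05 (the 0.05 is assumed), 3,000 runs per setting.

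- *Set-up of step 3, ultrasound a candidate.* MRI stayed in 5.7/8.8/13.1 % of runs at 70/80/90 % overlap with n = 69, and in 5.9/9.6/13.9 % with n = 80. MRI had the smaller univariable p-value in 3/8/14 % at n = 69. At 90 % overlap the two tests classify all 69 infants identically with probability (1 − 2×10×0.1/86)^69 ≈ 0.20. The order is then arbitrary, and these rates assume that ties go to ultrasound.
- *Same set-up, ultrasound left out.* MRI was significant in 84–85 % (n = 69) and 89 % (n = 80).
- *Continuous set-up.* Assumed: n = 80, CP 10.2 %, a baseline risk index with odds ratio 2 or 3 per SD, sex with odds ratio about 1.65, and a scan with no effect of its own.

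| Correlation of scan with baseline index | Baseline offered, stepwise | Baseline left out | Baseline forced in first |
|---|---|---|---|
| 0 | 5 % | 5–6 % | 6–7 % |
| 0.3 | 5–6 % | 9–13 % | 6 % |
| 0.5 | 7 % | 15–27 % | 6–7 % |
| 0.7 | 10 % | 25–46 % | 6 % |

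Where the worthless scan stayed in the stepwise model, whole-model apparent sensitivity averaged 0.82–0.86 and specificity 0.72–0.80 at the best cut-off. Adding that scan to the baseline model raised apparent AUC by only about 0.02.

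**The case against.** A reader might infer that a scan adding nothing would be reported as predictive, or that the stated analysis cannot address added value at all. The documents support neither reading. The likelihood ratio test at each step is a nested test of added value, perinatal covariables are provided for, and effect estimates with 95 % intervals are promised. If MRI and ultrasound both stay, the joint model gives MRI adjusted for ultrasound whatever the entry order. With routine data as candidates, a redundant scan is usually dropped. It is retained often only if those variables are left out, which the covariable sentence permits but does not plan.

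The 90 % result in step 3 is an unadjusted contrast on assumed inputs, built so that MRI is worthless. The protocol uses that contrast only to set the sample size.

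It can also be said that no aim claims incremental value over ultrasound, and that a base model with block entry is detail for an analysis plan that is not shown. This stands in part. But the article does not leave the matter open: it states the entry rule and the model whose accuracy is reported. A plan that followed that text would not produce the added accuracy. Finally, with so few CP cases any accuracy difference for CP will be imprecise, which is true and limits the remedy.

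**Conclusion.** The point holds in a limited form. The added predictive value of 30-week MRI or examination over gestation, sex and cranial ultrasound is not secured. The comparator in the stepwise test is set by p-value order, routine variables are not forced in, and no change in accuracy is produced. Accuracy owed to routine data could therefore be credited to the early assessments.

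The size depends on a choice the text leaves open. A scan of no added value is kept in about 5–14 % of simulated studies when routine variables compete. When they are left out, it is significant in 5–46 % (continuous set-up) or 84–89 % (ultrasound-only set-up). All these figures rest on assumed effect sizes, overlaps and a 0.05 retention level, and are illustrative. The roughly 90 % figure for the unadjusted contrast shows only that the contrast used for sample size cannot establish added value.

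**What to change.** For the third primary aim:

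- Fix a base model of gestation at birth, sex and worst ultrasound grade up to the date of the early scan, and keep it in every model. Later ultrasounds must stay out, since neonatal data are gathered until discharge.
- Add the 30-week MRI block and the 30-week examination block to that base.
- Report the likelihood ratio test for each block, the accuracy of base and of base plus block, and the difference with a confidence interval. Correct for optimism, since even a worthless scan raised apparent AUC by about 0.02.
- Use the continuous 12-month motor scores as the main test of added value. For CP, with about 7–8 cases, use a penalised model and label it exploratory.

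The cost is wording in the analysis plan. The variables are already collected, and the readers' planned blinding to gestation and ultrasound suits the comparison. The dates of the ultrasounds are needed if they are not already recorded. The downsides are imprecise CP estimates and probably less favourable claims for MRI alone.

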## Discussion

To our knowledge, this protocol describes the first study examining the clinical correlates of early advanced brain imaging and clinical measures at 30 weeks PMA to predict motor and neurodevelopmental outcomes at 3 and 12 months CA.

The results of this study will i) establish the relationships between early clinical measures, EEG, perinatal variables and nutrition and early advanced neuroimaging at 30 weeks PMA, ii) establish which components of brain structure and function most accurately predict neurodevelopmental, motor outcomes and CP at 3 and 12 months CA, iii) accurately identify infants at risk of adverse outcomes at an earlier stage, introducing an additional window of opportunity for intervention, iv) contribute to understanding brain development between 30 and 40 weeks PMA, v) and develop robust quantitative biomarkers of brain maturation, which can then be used in the research of interventions in this population.

## Abbreviations

AIMS: Alberta Infant Motor Scale
ASL: Arterial Spin Labelling
Bayley III: Bayley Scales of Infant and Toddler Development, version III
CA: Corrected age
CBF: Cerebral blood flow
CI: Confidence interval
CP: Cerebral palsy
CUS: Cranial Ultrasound
DTI: Diffusion Tensor Imaging
DWI: Diffusion Weighted Imaging
EEG: Electroencephalography
GA: Gestational age
GMs: General Movements Assessment
HARDI: High Angular Resolution Diffusion Weighted Imaging
HNNE: Hammersmith Neonatal Neurological Examination
IVH: Intraventricular haemorrhage
MND: Minor neurological deficit
MR: Magnetic resonance
MRI: Magnetic resonance imaging
NNNS: NICU Neonatal Neurobehavioural Scale
NSMDA: Neuro Sensory Motor Development Assessment
PMA: Postmenstrual age
PVL: Periventricular leukomalacia
TEA: Term equivalent age
TIMP: Test of Infant Motor Performance
